
### Outcome measures

The primary outcome measure is length of hospital stay, measured in minutes from the documented time of admission to the documented time of discharge (or censoring). These times are determined and entered into the patient’s electronic medical record by bed allocation staff who are blinded to the intervention. The secondary outcome measures are days and duration of antibiotic therapy. The start and stop dates corresponding to antibiotic administration while the patient is admitted to hospital are entered into the patient’s electronic medical record by pharmacy assistants who are blinded to the intervention. All inpatient antibiotic administration is verified through the paper-based medical administration record by a pharmacy assistant blinded to the intervention. The number of days of antibiotic therapy is defined as the total number of days of all antibiotics administered to the patient both while in hospital and after discharge. The duration of antibiotic therapy is defined as the number of days that the patient received antibiotics both while in hospital and after discharge. For example, if a patient received two antibiotics for 4 days over the same time period, then the days of antibiotic therapy is 8 days and the duration of antibiotic therapy is 4 days. The relevance of collecting both days and duration of therapy is that days of therapy is considered a valid metric for monitoring and comparing antibiotic utilization both within and across hospitals, whereas duration of therapy is necessary for determining adherence with best-practice treatment guidelines [30]. All antibiotic data from discharged patients will be extracted (by LM or GD) from the physician discharge summary and all patients will be contacted 30 days after discharge to verify their adherence with the prescribed antibiotic record from the discharge summary. Other secondary outcome measures include inadvertent adverse outcomes of readmission and mortality 30 days after discharge from hospital. Readmission to hospital is determined through telephone survey with the patient and verification through the Royal Victoria Regional Health Centre patient database. Survival is determined through telephone survey with the patient. The status of patients who cannot be reached by telephone will be verified through the Ontario vital statistics registry.

### Participant timeline

Enrollment of patients started 1 April 2013. The study is expected to enroll patients until 31 March 2015. All consecutive patients who meet the inclusion criteria and have no exclusion criteria will be eligible for the intervention. The ASP-i intervention may be implemented any time from 48 hours after admission in those patients who meet the criteria for ASP review. All patients who have not experienced an outcome measure at 14 days after admission will be censored from the study. Patients who die or are transferred from the ward (to the intensive care unit or other hospital) will also be censored. Patients who are discharged from hospital and are not censored will be contacted 30 days after discharge to determine their adherence with antibiotic prescription (if relevant), survival status, and readmission status.

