### Population

Starting 1 April 2013, all consecutive adult patients (≥18 years old) with the following inclusion criteria will be screened for enrollment in the study [5]:Screen positive for febrile respiratory illness on admission to hospital [24], andDiagnosed with pneumonia by the admitting physician (acute exacerbations of chronic obstructive lung disease are considered within the definition of pneumonia for the purposes of this study, as they are commonly treated with the same antimicrobial regimens as patients with pneumonia), andAdmitted to a medical ward.

All patients who meet these criteria will be eligible for the intervention except for those with the following exclusion criteria [5]:Hospitalized for ≥48 consecutive hours in the preceding 3 months, orReceiving immunosuppressants (defined as ≥40 mg prednisone daily, or steroid equivalent, for ≥2 weeks preceding hospitalization or any other immunosuppressant used for systemic illness or to prevent transplant rejection), orNeutropenic (defined as a polymorphonuclear count ≤0.5 × 10^9^ cells/l) for any cause, orImmunocompromised (defined as having leukemia, lymphoma, HIV with CD4 cell count ≤200, splenectomy or receiving cytotoxic chemotherapy), orAdmitted to high-acuity units, such as intensive care units, orRequire mechanical ventilation, either non-invasive or invasive, orHave a life expectancy of ≤3 months (palliative).

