### Sample size

The sample size expected for the current study is ‘fixed’ and has been previously estimated at between 400 and 500 CAP patients per calendar year [31]. The accrual period will be 24 months. Assuming that 70 % of patients in the control arm will achieve the primary outcome of being discharged alive from hospital, and setting power = 0.8 and statistical significance (two-sided) α = 0.05, the detectable ASP-i effect size is estimated to be up to an approximately 20 % reduction in length of stay [32]. The *stpower cox* command in STATA/MP 13.1 for Mac will be used for the calculation. 

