### Recruitment

All consecutive immune-competent adult patients admitted to a hospital ward with a diagnosis of CAP will be enrolled in the study, to ensure maximum enrollment.

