### Statistical methods

An extended Cox regression analysis that models the ASP-i as a time-variant covariate will be used to compare the primary and secondary outcome measures between the control and intervention groups [34]. Violations of the proportional hazards assumption for each covariate will be identified using the method of Schoenfeld residuals combined with the graphical method of log-log survival curve analysis [34]. Results will be reported as hazard ratios with 95 % confidence intervals. Patients who remain in hospital beyond 14 days will be administratively censored. Competing events, such as death or transfer from a medical ward to a critical care unit will be assumed to be non-informative conditional on the covariates included in the final model [34]. Time to ASP-i will be modeled as a time-variant covariate in the final model to account for any time-dependent bias [23]. The ASP-i exposure will be coded as a dichotomous variable; 0 = no ASP-i, switching to 1 = ASP-i at the time of the ASP-i and remaining 1 throughout the remainder of the follow-up time. This method treats a patient who has received an ASP-i as a non-ASP-i patient prior to the intervention. Other variables known to be associated with the primary and secondary outcome measures will also be included in the final model [5], and include; age, sex, Charlson comorbidity index, CURB-65 score, time (days) to clinical resolution, and complications from pneumonia, such as empyema. Fixed effects of wards on the outcomes will accounted for by including them as indicator variables in the final model. Maturation of ASP-i effect on outcomes over time will be adjusted by including a categorical time variable in the final model (time variable will be defined as ‘quarter’ from start of study). A dichotomous variable for acceptance or rejection of the ASP-i will be part of an interaction term with the control/intervention group variable to permit a per-protocol analysis. Sensitivity analysis will be done using a competing events Cox regression model to determine the impact of the assumption of the non-informative nature of events, such as death and admission to an intensive care unit [35].

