### Monitoring

The hospital administration requires quarterly reporting of primary and secondary outcome variables. Secondary adverse outcome measures such as mortality and readmission rates to hospital within 30 days after discharge will be monitored in real-time by preprogrammed calculation of relative risk ratios adjusted by the LACE score [36]. Relative risk ratios >1.2 for death or readmission at 30 days post-hospital discharge for the intervention group will be used to notify the hospital administration that an inadvertent adverse event might be due to the intervention, and an external safety monitoring committee of the Hospital Pharmacy and Therapeutics committee will be responsible for auditing the program. This relative risk ratio was chosen by the hospital administration as a reporting trigger.

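### Patients discharged before 48 hours can never receive the ASP-i, and the plan does not say which group they belong to in the 30-day safety comparison and its relative-risk trigger

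*Protocol article*

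**What the plan says.** All references are to the Protocol article.

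- **Who enters.** Recruitment: "All consecutive immune-competent adult patients admitted to a hospital ward with a diagnosis of CAP will be enrolled in the study". Population: "All patients who meet these criteria will be eligible for the intervention except for those with the following exclusion criteria". No exclusion concerns a short index stay; the 48-hour criterion listed there is about earlier hospitalization.
- **When exposure can start.** Participant timeline: "The ASP-i intervention may be implemented any time from 48 hours after admission in those patients who meet the criteria for ASP review".
- **How exposure is coded.** Statistical methods sets the ASP-i to 0 until it is received, "switching to 1 = ASP-i at the time of the ASP-i and remaining 1 throughout the remainder of the follow-up time". The same section applies this model beyond length of stay: "An extended Cox regression analysis that models the ASP-i as a time-variant covariate will be used to compare the primary and secondary outcome measures".
- **Safety outcomes.** Outcome measures lists readmission and mortality 30 days after discharge. Monitoring sets a LACE-adjusted trigger: "Relative risk ratios >1.2 for death or readmission at 30 days post-hospital discharge for the intervention group will be used to notify". It does not define the intervention group.
- **Sample size.** "Assuming that 70 % of patients in the control arm will achieve the primary outcome of being discharged alive from hospital", with 400 to 500 patients a year for 24 months, 80% power and two-sided 5% significance, giving a detectable effect of about 20%. No allowance is made for discharges that occur before exposure is possible.

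**The concern.** A patient who goes home at 30 hours is enrolled and followed but is unexposed by rule, in every ward and at every stage of the roll-out. Length of stay is analyzed from admission with time-varying exposure, which deals with this. The 30-day outcomes start their clock at discharge, when each patient's exposure is already fixed, so time-varying coding cannot help.

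The assignment of early discharges then depends on a definition that Monitoring does not give. If the groups follow receipt, as the coding in Statistical methods suggests, all early discharges are controls. If those patients have fewer deaths and readmissions, the ASP-i group looks worse with no effect present. At stake are the safety half of the research question and a trigger calculated in real time during the trial. A lesser issue is that early discharges count toward the 70% event assumption but carry no information on the ASP-i effect.

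**Working it through.** **1. The plan's own figure.** Inputs from Sample size: 800 to 1000 patients over 24 months, 70% discharged alive, 80% power, two-sided 5%. The exposed share is not stated; 1:1 is assumed. With D events, the Schoenfeld detectable hazard ratio is exp(−2.802/√(0.25·D)), where 2.802 = 1.960 + 0.842.

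- N = 800: D = 560, HR 0.789
- N = 900: D = 630, HR 0.800
- N = 1000: D = 700, HR 0.809

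The figure of about 20% reproduces if read as a hazard ratio of 0.80 (1.25 for discharge).

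**2. The same figure counting only discharges after 48 hours.** Let f be the share of discharges that occur before 48 hours. The documents do not give it. At N = 900:

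- f = 10%: D = 630 × 0.90 = 567, HR 0.790, power for HR 0.80 falls from 80% to 76%
- f = 20%: D = 630 × 0.80 = 504, HR 0.779, power 71%

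At N = 1000 and f = 10%, 630 events remain and power is 80%.

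**3. Is the length-of-stay hazard ratio biased?** No. Before 48 hours everyone at risk has ASP-i = 0, so those risk sets contribute nothing to its coefficient. In a simulated set of 900 patients with 854 discharges, the unadjusted time-varying Cox fit gave log HR 0.03234 (SE 0.08521). Dropping the 182 discharges before 48 hours left both values unchanged.

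**4. The safety contrast if groups follow receipt, with no true effect.** Let e be the share of ward-months in the active phase. With wards starting at months 3, 5, 7 and 9 of 24, e = (21 + 19 + 17 + 15)/96 = 0.75, assuming equal wards. Let c be the share of active-phase patients staying past 48 hours who receive the ASP-i, and r the 30-day risk of early discharges relative to the rest. Both c and r are assumptions. Then:

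- early share of the control group: s = f/[1 − e·c·(1 − f)]
- null relative risk = 1/[1 − s(1 − r)]

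Example with f = 10%, c = 1, r = 0.5: s = 0.10/0.325 = 0.308, and RR = 1/(1 − 0.154) = 1.18.

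| f | s (c = 1) | RR, c = 1, r = 0.5 | RR, c = 1, r = 0.75 | RR, c = 0.6, r = 0.5 |
|---|---|---|---|---|
| 5% | 17% | 1.10 | 1.05 | 1.05 |
| 10% | 31% | 1.18 | 1.08 | 1.09 |
| 15% | 41% | 1.26 | 1.12 | 1.14 |
| 20% | 50% | 1.33 | 1.14 | 1.19 |

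These are crude values. With r = 1 every entry is 1.00.

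**5. The safety contrast if groups follow ward-period.** Early discharges fall in both groups, so the null relative risk from this source is 1.0. They dilute a true effect only slightly. Assume 30-day risks of 6% (early) and 14% (others), and a true relative risk of 1.25 in the others. The observed value is [f·0.06 + (1 − f)·0.14·1.25]/[f·0.06 + (1 − f)·0.14], which is 1.24 at f = 10% and 1.22 at f = 25%.

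**The case against.** The strongest reply is that enrolling all admissions is a deliberate pragmatic choice, the primary analysis is sound, and the safety problem exists on only one reading of an undefined term. Study design speaks of contemporaneous controls, which fits a ward-period comparison, and on that reading the null relative risk is 1.0. On the receipt reading, the size rests on inputs that the documents do not give, and two of the three scenarios in the table never reach 1.2. The planned figure is also not crude: Monitoring adjusts by LACE, and Statistical methods lists age, comorbidity, CURB-65 and time to clinical resolution among its covariates. Crossing the trigger leads to notification and an audit, not to stopping.

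Most of this stands, and it limits the point. It does not remove it. Receipt is the better-supported reading: exposure is coded by receipt for primary and secondary outcomes alike, and the acceptance-or-rejection interaction presupposes a recommendation. Adjustment may narrow the imbalance, but it cannot supply exposed patients among those discharged before 48 hours.

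A reader might infer four stronger things that the documents do not support:

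- That length of stay is biased. Step 3 shows otherwise, and starting the risk period at 48 hours would leave the unadjusted ASP-i estimate unchanged.
- That early discharges are known to be low-risk, or that the trigger will be crossed. Neither their risk nor their number is given.
- That a real harm would be hidden. On the receipt reading the bias goes the other way; on the ward-period reading the dilution is 0.01 to 0.03.
- That the study is seriously underpowered for this reason. The loss in step 2 is modest.

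**Conclusion.** The point holds for the 30-day safety comparison and the trigger, conditionally on how the groups are formed. Patients discharged before 48 hours are enrolled, cannot be exposed, and are controls by rule if receipt coding is carried over. If they are at lower risk, the crude relative risk with no effect lies at about 1.05 to 1.33. That range assumes early-discharge shares of 5 to 20%, early risk at half to three-quarters of the rest, and 60 to 100% of longer-staying active-phase patients reached. Values above 1.2 occur only in part of it, and before adjustment. The consequence is a possible false alarm. The length-of-stay hazard ratio is unaffected. The detectable effect in Sample size is slightly optimistic, by about 0.01 to 0.02 on the hazard-ratio scale at 900 patients for early shares of 10 to 20%.

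**What to change.** - **Monitoring, and the 30-day outcomes in Statistical methods:** define the intervention and control groups by whether the ward was in its active or control period at admission. Restrict both groups to eligible patients still on a medical ward at 48 hours. Use these groups for the real-time relative risk.
- **Do not rely on the 48-hour restriction alone.** With groups by receipt, a patient in an active ward who leaves at 55 hours before being reviewed would still count as a control, so some of the selection would remain.
- **Report discharges before 48 hours separately,** by ward-period.
- **Sample size:** state that only discharges after 48 hours inform the ASP-i effect, and restate the detectable effect on that count with the assumed early share shown.
- **Primary analysis:** no change is needed for this reason.

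The cost is wording and a change to the preprogrammed calculation. Admission and discharge times are already recorded to the minute. The analyzed number becomes smaller, and the safety results apply to patients still in hospital at 48 hours. Because ward-period follows calendar time, the planned ward and quarter terms should be kept in the 30-day model.

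### For patients still in hospital at day 14, censoring from the study conflicts with antibiotic outcomes defined as the whole course and with 30-day contact of all patients

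*Protocol article*

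**What the plan says.** All references are to the Protocol article.

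- **Outcome definitions (Outcome measures).** Days of therapy is the "total number of days of all antibiotics administered to the patient both while in hospital and after discharge". Duration is "the number of days that the patient received antibiotics both while in hospital and after discharge". Neither definition has a day-14 limit.
- **30-day contact (Outcome measures).** "all patients will be contacted 30 days after discharge to verify their adherence with the prescribed antibiotic record from the discharge summary".
- **Censoring (Participant timeline).** "All patients who have not experienced an outcome measure at 14 days after admission will be censored from the study". Also: "Patients who die or are transferred from the ward (to the intensive care unit or other hospital) will also be censored".
- **30-day contact again (Participant timeline).** "Patients who are discharged from hospital and are not censored will be contacted 30 days after discharge to determine their adherence with antibiotic prescription". The sentence goes on to cover survival and readmission.
- **Censoring again (Statistical methods).** "Patients who remain in hospital beyond 14 days will be administratively censored". The same section applies the extended Cox model to the primary and secondary outcomes alike and sets no separate censoring rule for the antibiotic outcomes.

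**The concern.** The 14-day limit suits a length-of-stay analysis. The text, however, takes patients out of the study as a whole, and the follow-up sentence acts on that by dropping censored patients from the 30-day contact. For anyone still in hospital at day 14, this contradicts the definition of the antibiotic outcomes and the statement about who is contacted.

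Three things are at stake.

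- **Antibiotic outcomes.** Long courses are a direct target of the intervention: stopping antibiotics and duration of therapy are both on its list of possible recommendations. Days and duration of therapy are named in the research question.
- **Comparability.** Whether a course is observed to its end depends on discharge by day 14. Discharge is the primary outcome and is what the intervention is meant to bring forward, so completeness of antibiotic data can differ between exposed and unexposed patients.
- **Safety outcomes.** Mortality and readmission at 30 days after discharge are the planned check for harm, and the Monitoring section attaches a relative-risk trigger to them. Under Participant timeline, long-stay patients are not contacted for either.

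**Working it through.** **1. The plan's own figure.** The only related calculation is the sample size, which concerns length of stay. Inputs from Sample size: power 0.80, two-sided alpha 0.05, 70% of controls discharged alive, 400 to 500 patients a year for 24 months (800 to 1,000). No exposure split is given, so I assume 1:1. By Schoenfeld's formula, events = 4 × (1.960 + 0.842)² / (ln 0.80)² = 631, and 631 / 0.70 gives 902 patients. The detectable hazard ratio is 0.789 with 800 patients (560 events) and 0.809 with 1,000 (700 events). The stated effect of about 20% reproduces, and nothing below changes it.

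**2. Three patients followed through the text.**

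| Patient | Outcome measures | Participant timeline and Statistical methods |
|---|---|---|
| In hospital 18 days on one drug, 3 more days at home | Duration 18 + 3 = 21 days; contacted at 30 days | Censored at day 14; not contacted |
| Discharged day 9 with 7 days prescribed | Duration 9 + 7 = 16 days; contacted | Not censored, because discharge has occurred; contacted; 16 days |
| Antibiotics stopped day 7, still in hospital day 14 | Duration 7 days; contacted | Course already complete; no antibiotic data lost; not contacted |

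The sections disagree on the first and third patients and agree on the second.

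**3. Why the cut-off is plausibly informative.** After day 14, the patients still under observation for antibiotic duration are those already discharged. Remaining in hospital is plausibly related to remaining on antibiotics, so the censored patients are unlikely to resemble those who stay in the risk set. Statistical methods states a non-informative assumption, and plans a competing-events sensitivity analysis, for events such as death and transfer to critical care. It does neither for the 14-day rule.

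**4. Days of therapy.** This outcome adds up across drugs. A cut at calendar day 14 falls at 14 × 1 = 14 drug-days for a patient on one drug throughout and at 14 × 2 = 28 for a patient on two. On the drug-day scale, the censoring point therefore depends on how fast the patient accumulates the outcome, even if censoring were independent on the calendar scale.

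**5. How many patients.** If the control-arm 70% applied to everyone, 30% would not be discharged alive within the observation window: 0.30 × 800 = 240 and 0.30 × 1,000 = 300. These figures combine the 14-day limit, death and transfer, and the split is not given. They are therefore an upper bound on patients censored by the 14-day rule, and a looser one on patients who lose antibiotic data.

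**6. Illustration under assumptions.** Suppose 5% to 30% of patients are in hospital at day 14 and average 2 to 6 further antibiotic days. The unobserved amount, averaged over all patients, is 0.05 × 2 = 0.1 to 0.30 × 6 = 1.8 days. Neither range comes from the document, and the upper end needs the whole 30% to be long stays. The plan reports hazard ratios, so this gauges lost observation and is not a bias in the reported estimate.

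**The case against.** The strongest defence is that the rule is narrower than it first looks. A reader might infer from Participant timeline that every course is cut at day 14, including that of a patient discharged on day 9. The document does not support this. Statistical methods ties the rule to remaining in hospital, a patient discharged by day 14 has had the primary outcome, and post-discharge antibiotics come from the discharge summary and the 30-day contact. This part of the defence stands in full.

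A reader might also infer that long-stay patients are dropped from the antibiotic analysis. They are not: in a Cox model a censored patient contributes up to day 14, and only what follows is lost. That stands too. It does not remove the problem of a censoring point that depends on discharge.

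Third, being in hospital at day 14 is not the same as being on antibiotics at day 14, so counting all long-stay patients as affected would overstate the loss of antibiotic data. This also stands.

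Fourth, Outcome measures puts no 14-day limit on the inpatient antibiotic record and plans to contact everyone, so the data may be collected anyway. This makes the repair cheap, but it does not settle which data are analysed or which contact rule is followed.

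Finally, an article may leave outcome-specific censoring to a fuller document. Here, though, the article itself fixes the outcome definitions, the censoring rule and the contact population, and these disagree.

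**Conclusion.** The point holds for patients still in hospital at day 14 and for secondary outcomes only. For them, censoring from the study contradicts both the whole-course definitions and the contact of all patients. Followed as written, it cuts off antibiotics after day 14 and removes the 30-day survival and readmission contact. The cut-off depends on discharge, so it may differ by exposure and is plausibly informative, most clearly for days of therapy. The document does not allow the direction or size of any bias to be stated.

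The number affected is unknown. The bound of 240 to 300 patients assumes that the control-arm 70% applies to all 800 to 1,000 and includes deaths and transfers; antibiotic data are lost only for those still on antibiotics after day 14. Patients discharged by day 14, the length-of-stay analysis and the sample size are unaffected.

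**What to change.** Reconcile Outcome measures, Participant timeline and Statistical methods as follows:

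- State that the 14-day administrative censoring applies to the length-of-stay analysis only.
- For patients staying beyond 14 days, count antibiotics from the existing inpatient record to actual discharge, plus the discharge prescription.
- Apply the 30-day contact for antibiotics, survival and readmission to all patients discharged alive.

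The cost is amended wording, a little more extraction from records already kept, and a few more calls. One small downside is that some long courses will reflect problems other than the initial pneumonia. The change concerns measurement and analysis only and leaves patient care as it is.
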